## **Rationale**

### *Diagnostic and therapeutic relevance of predicting ovarian cancer preoperatively:*

The pre-operative assessment of adnexal tumours remains a major challenge for clinicians. Advances in surgery have provided more treatment options, but their potential usefulness depends upon a prior assessment of the mass using non-invasive procedures. It is often difficult to determine pre-operatively the nature (benign or malignant) of ovarian tumours. However, this knowledge is essential for obtaining a reliable diagnosis and for an appropriate management, both of which will influence the outcome for the patient and the medical costs. In case of benign functional cysts a laparoscopy or any other surgical intervention should be avoided in order not to create unnecessary morbidity and impaired fertility. On the contrary, most benign non-functional tumours can be treated laparoscopically or with a low transverse abdominal incision. Patients with a suspect adnexal mass require a series of expensive and unpleasant staging examinations and in most cases also an exploratory laparotomy through a median incision is indicated, because the rupture of a stage 1 ovarian cancer during the operation may worsen the prognosis. This procedure should only be performed by a surgeon with proper skills and experience in debulking surgery, since the amount of residual malignant tissue after primary surgery is one of the most important prognostic factors in ovarian cancer. Furthermore, appropriate pre-, per-, and postoperative measures should be taken.

During recent years several techniques have been introduced to differentiate between benign and malignant ovarian lesions. These techniques include serum tumour markers, transvaginal ultrasonography with a variety of morphological scoring systems, or sometimes combined with colour Doppler sonography, computerised tomography (CT scan), and magnetic resonance imaging (MRI). Despite numerous publications on each of these techniques, an insufficient amount of data is available to provide for a rational clinical management.

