### Task 6.1: Data collection

At least 2,000 new patients with persisting adnexal tumours will be examined. This results in a collection of roughly 300 difficult masses. The hypothesis is that adding the prediction by the model, developed for this specific subgroup of tumours, to the decision tree allows a significant reduction in the number of exploratory laparotomies for benign tumours when compared to the standard hospital procedure. Therefore, cases where the clinicians state to be uncertain about the diagnosis, will be randomised in two arms in 1:2 ratios:

- arm (A): standard hospital procedure approach
- arm (B): standard hospital procedure approach + result of difficult tumours model.

So, we will have roughly 100 cases in the control arm (arm A) and 200 cases in the model arm (arm B).

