### Task 6.2: Validation of the model

In both arms, the sensitivity and specificity will be calculated and compared. An increase of 10% specificity in the model arm (arm B), at an equivalent sensitivity in arm A and B, will be regarded as clinically relevant.

This analysis will be performed twice: 1) overall and 2) stratified by the degree of expertise of the ultrasound examiner. The 2nd analysis is planned due to the fact that less experienced ultrasound examiners might benefit more from the use of such model for difficult tumours than highly experienced investigators.

|                                        |
|----------------------------------------|
| Expertise in supporting centres |
|----------------------------------------|

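### WP6 requires equivalent sensitivity but fixes no tolerable loss, and the planned arms hold too few cancers to show equivalence reliably at any margin of 10 points or less

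*Protocol*

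**What the plan says.** Task 6.1 (Protocol, Work package 6) expects at least 2,000 patients: "This results in a collection of roughly 300 difficult masses". Cases in which the clinician is uncertain "will be randomised in two arms in 1:2 ratios", giving roughly 100 in arm A (standard hospital procedure) and 200 in arm B (the same plus the model result). The hypothesis is that adding the model "allows a significant reduction in the number of exploratory laparotomies for benign tumours".

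Task 6.2 describes the analysis: "In both arms, the sensitivity and specificity will be calculated and compared". The benchmark is a 10% rise in specificity in arm B which, "at an equivalent sensitivity in arm A and B, will be regarded as clinically relevant". The same comparison is then repeated by examiner expertise. No limit for the word equivalent is given, and the arm sizes follow from the expected yield of difficult masses, not from a count of cancers.

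The Rationale in section 2 explains why a suspect mass usually calls for exploratory laparotomy through a median incision: "because the rupture of a stage 1 ovarian cancer during the operation may worsen the prognosis". The opening of the literature section adds that a mass considered malignant should be referred to a gynaecologic oncologist.

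**The concern.** WP6 aims to reduce laparotomies for benign tumours by showing clinicians a prediction. The natural price of higher specificity is lower sensitivity, so the sensitivity condition is the counterweight to the benefit sought. Without a tolerable loss, nothing separates evidence of equivalence from a failure to see a difference. With few cancers, the second is easy to obtain.

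At stake is whether a model that wrongly moves malignant masses to benign could be reported as clinically relevant. A lost cancer here is a malignant mass misclassified before surgery. By the protocol's own account, that classification affects surgical route and referral.

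**Working it through.** **Plan's own figure.** Task 1.5 takes the 15% of masses nearest the LR1 decision boundary: 0.15 × 2,000 = 300. Split 1:2, this gives 100 and 200, so the stated arms reproduce.

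**Inputs not in the protocol.** It gives neither the malignancy rate nor the sensitivity among uncertain masses. Assumed ranges:
- Malignant: 25% (the overall IOTA 1 rate, 266/1,066) to 50%, since borderline tumours are over-represented among uncertain masses. This gives 25 v 50 to 50 v 100 cancers.
- Arm A sensitivity: 75% to 85%. This lies between the experts' 88-90% over all masses and their 60% (33/55) in borderline tumours.
- The 10% specificity gain is read as 10 percentage points.

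**Formulas.** With a and b cancers and common sensitivity s, SE = √[s(1−s)(1/a + 1/b)] and the 95% half-width is 1.96 × SE. Non-inferiority power at margin m (one-sided 0.025, truly equal sensitivities) is Φ(m/SE − 1.96). For 25 v 50 and s = 0.75: SE = √(0.1875 × 0.06) = 0.106, half-width 0.208, and power at m = 0.10 is Φ(0.943 − 1.96) = 0.15.

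The last two columns use exact binomial enumeration with a true 10-point loss in arm B: the chance that a pooled two-sided 5% z-test is not significant, and the chance that the observed loss is 5 points or less, counting exact 5-point losses.

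| Cancers A/B | Sensitivity A | Half-width (points) | Power at 5 / 10 / 15 points | Not significant | Observed loss ≤5 |
|---|---|---|---|---|---|
| 25/50 | 75% | 20.8 | 7 / 15 / 29% | 87% | 32% |
| 25/50 | 85% | 17.1 | 8 / 21 / 40% | 84% | 29% |
| 50/100 | 75% | 14.7 | 10 / 27 / 52% | 77% | 28% |
| 50/100 | 85% | 12.1 | 12 / 37 / 68% | 72% | 25% |

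**Both conditions together.** Suppose specificity truly rises 10 points from a baseline of 50-80% (assumed). Exact enumeration over 75 v 150 or 50 v 100 benign masses puts the chance of an observed gain of at least 10 points at about 0.52. Benign and malignant masses are separate patients, so the chances multiply:
- Sensitivity difference not significant: 0.52 × 0.72 = 0.37 to 0.52 × 0.87 = 0.45.
- Observed loss of 5 points or less: 0.52 × 0.25 = 0.13 to 0.52 × 0.32 = 0.17.

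**Cancers needed.** For a 10-point margin with 80% power at 1:2, arm A needs (1.96 + 0.842)² × 1.5 × s(1−s)/0.10² cancers: 151 at s = 0.85 and 221 at s = 0.75. That is 453 to 663 in total, against 75 to 150 expected.

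**Sensitivity of the result.** Over a wider range (26-50% malignant, sensitivity 60-90%) the half-width is 10-23 points. Power is 13-49% at a 10-point margin and 25-82% at 15 points.

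The count of 300 may itself be high. Task 6.1 randomises on clinician uncertainty, which the consortium section on O6 puts at 129/1,573 = 8% (90/1,066 plus 39/507). That is about 160 of 2,000, or 53 v 107. The same 10-point loss would then go undetected in about 83-92% of trials. The two definitions of a difficult mass need to be reconciled.

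**The case against.** The strongest reply is that test, interval and confidence level are usually left to an analysis plan, which is not shown. Task 6.2 prescribes no significance test, so reading equivalent as not significantly different is an inference. That stands for the method of testing. It does not dispose of the point, because the success criterion and arm sizes are fixed in the protocol and a margin written elsewhere cannot add cancers.

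The inputs are assumptions, and 60% in borderline tumours lies below the main sensitivity range. The wider range above leads to the same conclusion for margins of 10 points or less.

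Three stronger readings are tempting, and the documents do not support them:
- **That the design cannot show equivalence at all.** This depends on the margin. At 15 points, power reaches about 80% in the most favourable corner (50% malignant, 90% sensitivity).
- **That 72-87% is the chance of a wrong declaration.** That figure covers the sensitivity condition alone. Meeting the specificity condition as well brings it to 37-45%, or 13-17% if equivalent means an observed loss of 5 points or less.
- **That cancers would go undetected, with the sensitivity clause as the only protection.** Study patients have a histologically examined mass, arm B keeps the full standard procedure, and surgical route stays with the surgeon's judgement (section 8). The clause is the only stated statistical condition on sensitivity in WP6, not the only safeguard for patients.

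**Conclusion.** The point holds in this form: Task 6.2 fixes no tolerable loss of sensitivity, and the planned arms are unlikely to demonstrate equivalence at any margin of 10 points or less. With 25-50% malignant and arm A sensitivity of 75-85%, both assumed, non-inferiority power is 7-12% at 5 points, 15-37% at 10 and 29-68% at 15. A model that truly exchanged 10 points of sensitivity for 10 of specificity would satisfy a no-significant-difference reading of the rule in about 37-45% of trials. The split by examiner expertise divides the cancers further. This should be corrected before recruitment, because the rule as written can attach a claim of equivalent sensitivity to data that do not support one.

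**What to change.** In Task 6.2, replace the equivalence wording with a maximum tolerable loss of sensitivity, chosen by the Steering Committee before recruitment. Require the lower confidence limit of the sensitivity difference (B minus A) to lie above that loss. If it does not, report the sensitivity and specificity differences as estimates with confidence intervals, and claim neither equivalent sensitivity nor clinical relevance.

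This changes a sentence or two and needs no extra patients. Its real cost should be stated openly: at the planned size a margin of 10 points or less would usually not be met even by a harmless model, so WP6 will probably report estimates only.

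A listing of arm B malignancies reclassified as benign after the model was shown would be informative but is optional. Task 1.2 freezes the examiner's assessment before the model result appears, and the protocol does not describe recording a diagnosis after it. The listing would therefore need a new data item.

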### **Task 1.5: Patient selection for Second stage tests**

The IOTA 2 dataset enables us to describe the population characteristics of each centre in correlation with the performance of the models in that centre. This gives us the opportunity to define centre-specific cut-offs above which an adnexal mass is classified as malignant. Whenever the probability of malignancy is amongst the 15% that lies close to the decision boundary of LR1, the examiner will be obliged to perform one of the second stage tests. In this way, we expect that the adnexal masses of approximately 300 patients will be classified as “difficult” and will need a second stage test.

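### Task 6.2 asks whether less experienced examiners benefit more from the model, but the analysis it names repeats the arm comparison by expertise and never compares the benefit between expertise levels.

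*Protocol*

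**What the plan says.** Task 6.1 (Protocol, Work package 6) expects a fixed number of difficult masses from the 2,000 patients: "This results in a collection of roughly 300 difficult masses". It then says that "cases where the clinicians state to be uncertain about the diagnosis, will be randomised in two arms in 1:2 ratios", giving about 100 in arm A (standard approach) and 200 in arm B (standard approach plus the model result).

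Task 6.2 compares sensitivity and specificity between the arms. It regards a 10% gain in specificity in arm B, at equivalent sensitivity, as clinically relevant. It continues: "This analysis will be performed twice: 1) overall and 2) stratified by the degree of expertise of the ultrasound examiner". The second analysis is justified by the expectation that "less experienced ultrasound examiners might benefit more from the use of such model for difficult tumours than highly experienced investigators".

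Work package 6 names no test, significance level or set of expertise categories, and no comparison of one expertise level with another.

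**The concern.** The justification is a hypothesis of effect modification: the change from arm A to arm B is larger for less experienced examiners than for experts. Its null is that the change is the same at both levels. The named analysis looks at the change within each level, where the null is that there is no change at that level. These are different questions. A gain that shows in one stratum and not in the other is not in itself evidence that the gains differ.

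What is at stake is the reading of the expertise result. With about 300 masses split by arm, by expertise and by histology, stratum estimates will scatter widely. A reader who sets them side by side could see the expected pattern (helps the less experienced, not the experts) when the true gain is the same in both. The overall comparison is not affected.

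**Working it through.** **1. The plan's own figures.** Task 1.5 sends to second-stage tests the 15% of masses nearest the LR1 boundary: 0.15 x 2,000 = 300. A 1:2 split gives 300/3 = 100 in arm A and 200 in arm B. Both figures reproduce.

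**2. Question against analysis.** Write D for specificity in arm B minus specificity in arm A.
- Question in Task 6.2: is D(less experienced) - D(highly experienced) > 0?
- Analysis in Task 6.2: estimate D overall, then D within each expertise level.

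None of these estimates is the contrast in the question. If stratified is taken to mean one pooled, expertise-adjusted D, the contrast is still missing.

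**3. Assumptions not in the protocol.** Two equal expertise strata, 50-70% of difficult masses benign, arm A specificity 50-80%, two-sided 5% tests.

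**4. One setting by hand.** Take 60% benign, specificity 0.70 in arm A and 0.80 in arm B, the same in both strata. Each stratum has 30 versus 60 benign masses.
- SE of D in one stratum = sqrt(0.70 x 0.30/30 + 0.80 x 0.20/60) = sqrt(0.00967) = 0.098.
- 10-point mark: the true gain lies on the mark, so each stratum reaches it about half the time. P(exactly one) = 2 x 0.5 x 0.5 = 0.50.
- Significance: pooled proportion (21 + 48)/90 = 0.767; null SE = sqrt(0.767 x 0.233 x (1/30 + 1/60)) = 0.095. Power = P(Z > (1.96 x 0.095 - 0.10)/0.098), about 0.19. P(exactly one significant) = 2 x 0.19 x 0.81 = 0.31.
- Direct contrast: SE = sqrt(2) x 0.098 = 0.139, so the 95% half-width is 1.96 x 0.139 = 0.27, or 27 points. For a true difference of 10 points, 0.10/0.139 = 0.72, giving power of about 11%.

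**5. Over the range of assumptions** (200,000 simulated trials per setting, specificity only):

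| True gain in the two strata | Opposite sides of the 10-point mark | Significant in exactly one | Direct test of the difference rejects |
|---|---|---|---|
| 10 and 10 points | about 50% | 24-42% | about 6% |
| 0 and 0 | 23-36% | about 5% | about 6% |
| 5 and 15 points | 55-62% | 29-62% | 10-16% |

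In the first row, half of the 50% (about 25%) is the pattern in which only the less experienced stratum reaches the mark.

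**6. Precision of the direct contrast.** The 95% half-width is 1.96 x sqrt(2 x (pA(1-pA)/nA + pB(1-pB)/nB)), with a 10-point gain.
- 50% benign, pA 0.50: 1.96 x sqrt(2 x (0.25/25 + 0.24/50)) = 0.34.
- 70% benign, pA 0.80: 1.96 x sqrt(2 x (0.16/35 + 0.09/70)) = 0.21.

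So the interval is about +/-21 to +/-34 points.

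**7. If fewer are randomised.** The 300 rests on closeness to the LR1 boundary, whereas randomisation follows clinician-stated uncertainty. The consortium section on O6 puts the share that examiners found difficult at 8% in earlier phases: 0.08 x 2,000 = 160. With 160 masses and 50-75% benign, an equal 10-point gain is significant in exactly one stratum in 15-29% of trials, and the direct test rejects in 6-7%.

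**The case against.** The best defence is that the protocol leaves the details open. It gives no stratum decision rule and no number of levels, and a stratified analysis does not rule out an interaction test in a statistical analysis plan. That is fair as to detail. But Task 6.2 states both the question and the analysis meant to serve it, and the two do not match. A plan that simply carried out Task 6.2 would leave the question unanswered.

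Several stronger readings are tempting and are not supported:
- A reader might infer that each stratum will receive its own verdict and that use of the model will then be directed by expertise. No text says so. The 10% reads naturally as a smallest relevant difference, and the main question and hypothesis of work package 6 are not split by expertise.
- A reader might infer that applying the criterion again by stratum greatly raises the chance of a false success. The criterion also requires equivalent sensitivity, which a count based on specificity alone ignores, and no success claim is attached to strata. Nor does the text support more than the two groups it contrasts.
- A reader might infer that discordant strata point to equal effects. They do not: discordance is more frequent when effects differ (55-62% for gains of 5 versus 15 points, against 50% for equal 10-point gains).

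Two limits on the figures also stand. The 50% is what one expects when the true gain sits exactly on the mark. By significance, the problem arises only when the model has some effect; with none, discordance is about 5%.

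Finally, an interaction estimate from these numbers cannot settle the question. That is true, and it is a reason to show the imprecision openly.

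**Conclusion.** The point holds in a limited form. The stratified analysis in Task 6.2 is planned to learn whether benefit differs by expertise, but no reading of it compares the benefit between levels. If stratum results are set side by side, the same 10-point gain in both would look different by the 10-point mark in about half of trials and by significance in about 24-42%. A direct comparison would wrongly signal a difference in about 6%.

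These sizes rest on assumed strata, benign share and arm A specificity, on the planned 100 versus 200 masses, and on specificity alone. They also depend on a reader treating discordance as evidence, which the protocol does not itself prescribe. The mismatch between question and analysis depends on none of these assumptions.

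**What to change.** Amend Task 6.2 as follows:
- State that the overall arm comparison is the basis of the work package 6 conclusion.
- For expertise, estimate the arm by expertise interaction, that is, the difference between expertise levels in the arm B minus arm A change. Do this in benign masses for specificity and in malignant masses for sensitivity, each with a 95% confidence interval, and label it exploratory.
- Show the stratum estimates with confidence intervals as description, without judging each stratum against the 10% criterion.
- State that a non-significant interaction is not evidence of equal benefit.

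The cost is a change of wording and one extra model term on data already collected. The price in inference is that a claim of greater benefit for less experienced examiners becomes hard to make: power is about 10-16% for gains of 5 versus 15 points.

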#### **Division SCD, Department of Electrical Engineering (ESAT) of the Katholieke Universiteit Leuven.**

SCD's major research objective is to design and build advanced methods for crucial problems in information processing. It builds on the enormous growth in computer power, communication bandwidth and available data and the various needs in society for effective use of these opportunities. The strength of the group is the use of mathematical engineering/engineering mathematics from mathematical fields such as linear and multi-linear algebra, statistics, discrete mathematics, differential geometry, and optimization. In this way, SCD has built up world recognised expertise in bioinformatics, biomedical data processing, signal (audio, communications) processing, cryptography, embedded systems, data mining, neural networks, identification, control. Two research groups with complementary expertise within the Division of SCD, are participating in the project, i.e.

1. The **SCD/BIOMED** team consists of 1 staff member, 3 postdocs, 15 PhD students. Research – fundamental/theoretical as well as application oriented- is performed in the domain of (multi)linear algebra, (non)linear signal analysis, classification and system identification with special focus to the development of numerically reliable and robust algorithms for improving medical diagnostics. In this domain the group has built up an international reputation (more than 150 publications, look <http://www.esat.kuleuven.ac.be/sista/>). Applications under study are: quantification of metabolite concentrations using in-vivo Magnetic Resonance Spectroscopic (MRS) data and images, quantification of brain oxygenation in neonates using (functional) Near-Infrared Spectroscopy, quantification of cardiovascular dynamics and auto-regulation, heart-rate variability, detection of somato-sensory evoked potentials in EEG, preoperative classification of (brain, ovarian, prostate) tumours and prediction/detection of epileptic seizures based on scalp-EEG monitoring. At present, research focuses on the integrated multimodal and multichannel data processing, analysis and decision support for simultaneously acquired biomedical data such as EEG, ECG, EMG, (functional) MRI, ultrasound, PET and SPECT.
2. The **SCD/BIOI** group is one of the largest bioinformatics groups in Belgium with extensive internationally renowned experience in the integration of mathematical, statistical, and computational methods to analyze biological, biochemical, and biophysical data. The group is specialised in bioinformatics and more particularly in the analysis of large, complex data sets to identify biological and/or clinical relationships between different parameters. A high level of expertise in bioinformatics is a key element to successfully accomplish the goals of the current project proposal. Within the ESAT-SCD group, expertise in all necessary domains is present as well as the necessary hardware and software background. Our research focus is on gene prioritisation, gene network inference, motif detection and disease management, see [www.kuleuven.be/bioinformatics](http://www.kuleuven.be/bioinformatics) for more detailed information. SCD/Bioi operates internationally at the cutting edge of its frontline enabling discipline. The scope of its activities are regional, national and international.

Regarding **proteomics** the research in this project is performed in the Interfaculty Centre for Proteomics and Metabolomics (ProMeta) at the KU Leuven. ProMeta has cutting-edge wet-lab and in silico technologies.

